**Figure 3 F3:**
[figure not shown]
Schedule of assessment.

#### Baseline characteristics

Baseline demographics for each participant such as age, sex, body mass index, medical history, etc. will be obtained prior to surgery but after informed consent is given.

#### Perioperative findings

Intraoperative findings including operative time, estimated blood loss, incision length, intraperitoneal findings, method of appendiceal base ligation, additional port insertion, conversion to open appendectomy, and skin suture technique will be recorded. Postoperative analgesics use, hospital stay, and morbidities within 30 days after surgery will be also collected.

#### PROMs for postoperative pain

VAS and IPO will be used for comparing postoperative pain between treatment groups. VAS will be obtained 6 hours after surgery, as well as on the morning of postoperative day 1 and 2. IPO will be obtained on postoperative day 1.

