**Highlights:**

## Background

Acute appendicitis is one of the most common causes of emergency gastrointestinal surgery worldwide. Even though controversy regarding the medical management of acute appendicitis using antibiotics exists, appendectomy is currently considered the gold standard treatment.

Open appendectomy rather than laparoscopic appendectomy was performed universally until the 1990s, even though Kurt Semm, a German gynecologist, first introduced laparoscopic appendectomy firstly in 1983 [1]. Currently, most appendectomies are laparoscopic because of the advantages including early recovery, less pain, and improved cosmetic satisfaction compared with open appendectomy [2].

A conventional laparoscopic appendectomy (CLA) usually requires insertion of three port trocars with two working ports and one camera port. Additionally, single-incision laparoscopic appendectomy (SILA) has become popular since it was first introduced in 1992 [3]. Recent meta-analysis reported that SILA is a safe and feasible procedure compare to CLA, though SILA is a considered more technically demanding than CLA [4,5,6].

Theoretically, SILA would be expected to produce less pain, encourage faster recovery, and result in better cosmetic satisfaction than CLA. However, several previous reports comparing SILA and CLA have yielded conflicting results and only a few studies have reported that SILA is superior to CLA with respect to pain and/or cosmesis [7,8,9,10,11]. One randomized control trial (RCT) failed to show the superiority of SILA over CLA with respect to pain and cosmesis [12]. Furthermore, a recent meta-analysis reported no differences in the pain and cosmesis scores between SILA and CLA [5,13]. Several studies, rather, have even reported that postoperative pain is more severe after SILA than after CLA [14,15].

Previous RCTs compared between SILA and CLA used simple visual analog score (VAS) for the assessment of both pain and cosmetic satisfaction. Results originated from this type of assessment have limitations with regard to their objectiveness.

There are several patient-reported outcomes measures (PROMs) used for assessing the pain and cosmetic satisfaction after surgery including the International Pain Outcome (IPO) Questionnaire [16], the Patient and Observer Scar Assessment Scale (POSAS) [17], and the Body Image Questionnaire (BIQ) [18]. However, there is a paucity of literature reporting outcomes comparing SILA and CLA using these tools.

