### Randomization and sample size calculation

All participants will be randomized to either the SILA group or the CLA group in a 1:1 ratio. The randomization allocation will occur just to surgery using a computerized randomization system.

The target sample size will be 120 participants, as this will provide 80% power at the 2.5% (two-sided) level of significance to detect a three-point difference in the POSAS score between the SILA group and the CLA group at 6 weeks after surgery. Our target sample size allows for 10% attrition.

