### Endpoints

The primary trial endpoint is cosmetic satisfaction at 6 weeks after surgery as measured by POSAS. The secondary endpoints are cosmetic satisfaction assessed via BIQ, pain assessed via the IPO questionnaire and VAS, and the presence of general postoperative complications.

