### Statistical analysis

All analyses of the primary and secondary endpoints will be conducted with the intention-to-treat population. A per-protocol analysis will also be performed for further comparisons. Normally distributed data will be conducted with Student’s t test. Non-normally distributed data will be examined using the Mann-Whitney U test. The chi-square or Fisher’s exact test will be used to examine categorical variables. All analyses will be performed using the SPSS statistical package version 21.0 (Chicago, IL, USA) and statistical significance will be declared for tests with p values < 0.05.

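### Day-1 pain scores are tied to the calendar rather than to hours since surgery, which adds modest noise to a secondary endpoint; record clock times and adjust for elapsed time

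*Protocol article*

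**What the plan says.** The section on PROMs for postoperative pain sets the VAS schedule in one sentence: "VAS will be obtained 6 hours after surgery, as well as on the morning of postoperative day 1 and 2". The first score is defined by elapsed time and the next two by calendar morning. The next sentence gives the IPO a day and no time of day: "IPO will be obtained on postoperative day 1".

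The Endpoints section makes these secondary outcomes: "pain assessed via the IPO questionnaire and VAS, and the presence of general postoperative complications". The Statistical analysis section names two-group tests for continuous scores, "Normally distributed data will be conducted with Student’s t test", with the Mann-Whitney test as the alternative. It mentions no term for time since surgery.

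The Background calls appendicitis a leading cause of emergency operations: "Acute appendicitis is one of the most common causes of emergency gastrointestinal surgery worldwide". The article does not limit the hour of surgery, say when a morning reading is taken, or define how postoperative days are counted. The assessment schedule (Figure 3) is not reproduced in the text available.

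**The concern.** Pain changes over the first day or so after an operation. If operations end at different hours, a score taken the next morning catches patients at different points on that course. Someone whose operation ends just before midnight is scored on day 1 after about 8 h. Someone whose operation ends just after midnight is scored after about 32 h, which is also when the first patient gives the day-2 score. For the late-evening patient, the 6-hour score (about 06:00) and the day-1 score (about 08:00) are only some 2 h apart.

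Two things are at stake. Timing differences add between-patient variance that the named tests do not remove. The day-1 difference also becomes an average over a range of elapsed times, which is harder to interpret or to set beside other studies. This matters somewhat because pain reduction is one of the two comparisons the trial sets out to make, and the IPO is taken once, on the loosest timing of all.

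**Working it through.** The article gives no figure for elapsed time at the day-1 score, so there is nothing to reproduce. The check derives the spread and then its effect on variance.

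**Inputs from the article.** Scores at 6 h and on the mornings of days 1 and 2; IPO on day 1; 1:1 randomisation; 120 patients with 10% attrition, so 120 × 0.9 / 2 = 54 evaluable per arm.

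**Assumptions.** Morning reading at 08:00. Day 0 is the calendar day on which surgery ends. End times are uniform over the stated span. Mean pain decays from 5 with a half-life (HL) of 12, 18, 24 or 36 h. Other between-patient SD is 2.0 (1.5 as a check).

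**Step 1: elapsed time.** For surgery ending at clock hour *h*, elapsed time on day 1 is *t* = (24 − *h*) + 8 = 32 − *h*.
- Any hour (0 to 24): 8 to 32 h; day 2 is 24 h later, 32 to 56 h.
- Ending 08:00 to 24:00: 8 to 24 h.
- Ending 09:00 to 18:00: 14 to 23 h.
- Reading at 06:00 or 10:00 instead, any hour: 6 to 30 h or 10 to 34 h.

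**Step 2: variance from timing alone.** Expected pain is 5 × 0.5^(*t*/HL). For HL = 12 h over 8 to 32 h it runs from 3.15 to 0.79. Its mean is 1.704 and its mean square 3.355, so the variance is 3.355 − 1.704² = 0.451 and the SD 0.671. Variance inflation is 1 + 0.451/2.0² = 1.11. The other cases follow in the same way:

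| Score, end of surgery | Added SD, HL 12 / 18 / 24 / 36 h | Inflation at SD 2.0 |
|---|---|---|
| Day 1, any hour | 0.671 / 0.635 / 0.571 / 0.457 | 11 / 10 / 8 / 5% |
| Day 1, 08:00–24:00 | 0.545 / 0.486 / 0.423 / 0.328 | 7 / 6 / 4 / 3% |
| Day 1, 09:00–18:00 | 0.260 / 0.246 / 0.220 / 0.175 | 2 / 2 / 1 / 1% |
| Day 2, any hour | 0.168 / 0.252 / 0.285 / 0.288 | 1 / 2 / 2 / 2% |

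At SD 1.5 the first row becomes 20 / 18 / 14 / 9%.

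**Step 3: power.** Take an illustrative 1-point VAS difference, two-sided 5%, 54 per arm, and power = Φ(1/(σ√(2/54)) − 1.96).
- No timing variance, σ = 2.0: Φ(2.598 − 1.96) = 74%.
- Worst decay case, σ = √(4 + 0.451) = 2.110: Φ(2.463 − 1.96) = 69%.
- Day 1, any hour, across all four half-lives: 69 to 72%.

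**Step 4: a different pain curve.** With a straight-line fall of 0.05, 0.10 or 0.15 points per hour and end times uniform over 24 h (SD 24/√12 = 6.93 h), σ becomes 2.03, 2.12 or 2.25 and power 73%, 69% or 64%. The steepest slope means a fall of 0.15 × 24 = 3.6 points across the window, more than any of the decay curves gives (at most 3.15 − 0.79 = 2.36). It is an outer bound.

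**The case against.** The case against is substantial.

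- **Nothing is contradictory.** An early score timed from surgery followed by morning scores is a coherent and feasible schedule. It also gives a common time of day and ward routine, which elapsed-time scoring gives up.
- **Details may sit elsewhere.** A visit window, a time field or a covariate could be in Figure 3, the full protocol, the case report form or an analysis plan. Their absence from an article cannot be held against the trial. The point rests only on how the article itself times the scores and on the unadjusted tests it names.
- **A reader might infer that day-1 scores are generally spread over 8 to 32 h.** The article does not support that. The range is an extreme resting on an 08:00 reading, a midnight day count and surgery at any hour, none of which is stated. The Background sentence describes the disease worldwide, not operating hours at these centres. Daytime operating alone would give 14 to 23 h.
- **A reader might infer a biased comparison.** That does not follow either: "All participants will be randomized to either the SILA group or the CLA group in a 1:1 ratio", so hour of surgery is balanced in expectation and the planned tests remain valid. Chance imbalance remains, but it is already counted in the variance figures.
- **A reader might infer that two of the three VAS scores are redundant.** This applies only to operations ending near midnight, a share that the article does not give.
- **Fixed 24 h and 48 h scoring is not clearly better.** For surgery ending at 02:00, a window of 24 h ± 4 h runs from 22:00 to 06:00, so it can itself fall at night.

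All of this stands. It limits the point to noise and interpretability, mainly on day 1. It does not remove the gain from recording times and adjusting for them.

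**Conclusion.** The point holds as a minor one. The day-1 VAS and the IPO are tied to the calendar, and the article's named tests treat them as a single time point. Under the assumptions above, day-1 variance rises by about 1 to 11% at an SD of 2.0. The lower end corresponds to daytime operating and the upper end to surgery at any hour with a 12 h half-life. On day 2 the effect is negligible. For a 1-point difference, power falls from 74% to no lower than about 69% under the decay curves.

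No bias between arms is expected, and the primary endpoint and its sample size are untouched. The pain level, decay rates, SDs and end-time distributions are assumptions; the article gives none of them. A smaller SD or a steeper fall in pain would enlarge the effect, as the SD 1.5 and straight-line figures show. The IPO shares the weakness and lacks even a time of day.

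**What to change.** Keep the morning schedule. In the section on PROMs for postoperative pain, state that the clock time of surgery and of each VAS and IPO assessment is recorded, unless the case report form already does so. In the Statistical analysis section, adjust the day-1 VAS and IPO comparisons for time since surgery.

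Count that time from the start of surgery or from randomisation, not from the end of surgery. The end depends on operative time, which may differ between the two techniques, so adjusting for it would condition on something that the allocated procedure can affect.

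The cost is one time field on the form and one covariate in a secondary analysis. Moving the later scores to fixed 24 h and 48 h times is optional. It would narrow the spread to the width of the allowed window, but would give up a common time of day and could call for assessments at night.

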#### PROMs for cosmetic satisfaction

POSAS and BIQ will be obtained 6 weeks after surgery in the outpatient clinic. If any participant is unable to attend the clinic, a telephone interview will be permitted for completion of the survey.

#### Monitoring

All the data acquired for this study will be anonymized through the assignment of a trial identification number which will be used only for this study and accessed by only authorized persons. A study monitoring committee independent from the sponsor and investigator will check the study process and participants’ safety. Any adverse events related to the study will be reported to the study monitoring committee. All data will be stored for 3 years after completion of the study.

### Statistical analysis

All analyses of the primary and secondary endpoints will be conducted with the intention-to-treat population. A per-protocol analysis will also be performed for further comparisons. Normally distributed data will be conducted with Student’s t test. Non-normally distributed data will be examined using the Mann-Whitney U test. The chi-square or Fisher’s exact test will be used to examine categorical variables. All analyses will be performed using the SPSS statistical package version 21.0 (Chicago, IL, USA) and statistical significance will be declared for tests with p values < 0.05.

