## Methods

### Study design

This study is a multi-center, prospective, open-label, randomized trial. Patients diagnosed with acute appendicitis at participating centers will be screened for study enrollment. Enrolled participants will be randomly allocated to either the SILA group or the CLA group. This study follows the recommendations of the SPIRIT (Standard Protocol Items: Recommendations for Interventional Trials) guidelines. The study flowchart is shown in ***Figure 1***.

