This study has some limitations even though it was designed as a prospective multi-center RCT. First, there are no Korean validated versions of the PROMs which will be used. However, investigators discussed the bases of clinical similarity and significance of the original version and translated the PROMs into Korean. In addition, all PROMS will be administered under the guidance of investigators or trained clinical nurses. Second, we will not be specifying which appendiceal base ligation or wound closer method must be used and instead will leave these decisions to the surgeon’s preference. This may act as a source of bias affecting the results. However, all the participating surgeons are colorectal surgery specialists who have performed hundreds of laparoscopic colorectal resections including SILA and CLA techniques. As a result, surgical skill should have a minimal impact on postoperative morbidities between surgeons.

In summary, this study is a prospective multi-center RCT designed to compare SILA and CLA with regard to cosmetic satisfaction and postoperative pain. We believe that the results of this study will clarify the efficacy of SILA for the treatment of acute appendicitis and will be helpful for determining which patients would benefit from SILA instead of CLA.

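### The primary POSAS comparison is fixed as an unadjusted two-group test in a multi-centre trial: valid, but it leaves any between-centre variation in the error term

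*Protocol article*

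**What the plan says.** The Study design section states: "This study is a multi-center, prospective, open-label, randomized trial". The number of centres is not given. The Endpoints section states: "The primary trial endpoint is cosmetic satisfaction at 6 weeks after surgery as measured by POSAS". No scar score before surgery is described.

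The Statistical analysis section covers every endpoint: "All analyses of the primary and secondary endpoints will be conducted with the intention-to-treat population". The methods it names are all unadjusted two-group comparisons. For continuous outcomes, "Normally distributed data will be conducted with Student" introduces the t test, and "Non-normally distributed data will be examined using the Mann-Whitney U test". Categorical outcomes get chi-square or Fisher's test. No centre term, surgeon term or covariate appears.

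The Baseline characteristics section states: "Baseline demographics for each participant such as age, sex, body mass index, medical history, etc. will be obtained prior to surgery". The SILA section leaves skin closure (nylon, subcuticular suture or adhesive) to the surgeon, and the CLA section says that its other techniques are similar. On this freedom over ligation and closure, the Discussion says: "This may act as a source of bias affecting the results". The randomization section gives a 1:1 computerized allocation and does not say whether it is stratified.

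**The concern.** How the skin is closed plausibly affects a 6-week scar score. If surgeons at one centre favour one method, mean POSAS will differ between centres. It is an inference, though a reasonable one, that closure habits cluster by centre; the article does not say so.

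A pooled t or Mann-Whitney test counts such differences as noise. Two consequences follow. If centre explains part of the variance, the trial has less power than the same patients could give. If allocation was stratified by centre, the arms are balanced on centre by design but the test's standard error takes no credit for it, so the test is conservative. Neither consequence inflates the false-positive rate.

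**Working it through.** **1. The plan's own figure.** The article gives a total of 120, 10% attrition, a 3-point difference, 80% power and two-sided 2.5%, but no SD. Evaluable patients: 120 × 0.9 = 108, or 54 per arm. Solving for the SD by the normal approximation, SD = 3 / [(z for alpha + z for power) × √(2/54)]:

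- two-sided 2.5%: 3 / [(2.241 + 0.842) × 0.1925] = 5.06
- two-sided 5%: 3 / [(1.960 + 0.842) × 0.1925] = 5.56

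So 120 fits an unadjusted comparison with an SD near 5 at 2.5%. Going forward, SD 5.0 gives 53 per arm, 106 evaluable and 106/0.9 = 118 in total. Nothing here shows the figure of 120 to be wrong.

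**2. Power with adjustment.** SD 5.0 is an assumption taken from step 1. R² is the share of POSAS variance explained by centre and any covariates, also an assumption. The residual SD is 5.0 × √(1 − R²). The noncentrality is 3 / [residual SD × √(2/54)], which is 3.118 at R² = 0. The critical t on 106 degrees of freedom is 2.274 (2.5%) or 1.983 (5%). Both levels are shown because the sample-size text uses 2.5% and the analysis text uses p < 0.05.

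**3. Cost of the added terms.** Degrees of freedom alone cost less than 0.1 point of power. Chance imbalance costs more: if allocation is not stratified, k added terms raise the variance of the treatment estimate by about (N − 3)/(N − 3 − k) on average. With N = 108 this is 105/100 = 1.05 for k = 5 and 105/97 = 1.08 for k = 8.

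| Assumed R² | 2.5%: before cost | 2.5%: net, 5 terms | 5%: before cost | 5%: net, 5 terms |
|---|---|---|---|---|
| 0 | 79.9% | 77.7% | 87.1% | 85.4% |
| 5% | 82.1% | 80.0% | 88.7% | 87.1% |
| 10% | 84.3% | 82.3% | 90.3% | 88.8% |
| 20% | 88.5% | 86.8% | 93.2% | 92.1% |

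At R² = 0, the unadjusted test is the 79.9% or 87.1% entry. Five useless terms lose 2.2 points (79.9 − 77.7) at 2.5% and 1.7 points at 5%. Eight useless terms give 76.3% and 84.3%, a loss of 3.6 and 2.8 points. Break-even for five terms is near R² = 5/105 = 4.8%, and for eight near 8/105 = 7.6%. If allocation is stratified by centre, the centre terms are nearly balanced between arms and most of their cost disappears.

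**4. A different SD.** The 87.1% baseline depends on SD 5.0. If the design was really set at two-sided 5% (SD 5.56), the normal approximation gives 80.0% unadjusted and 82.0%, 84.0% and 87.9% at R² of 5%, 10% and 20%, before cost.

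**5. Conservatism under stratification.** If allocation is stratified by centre and centre explains a share R² of the variance, the large-sample true level of a nominal 5% test is 2 × [1 − Φ(1.960/√(1 − R²))]. That is 3.9% at 10% and 2.8% at 20%.

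**The case against.** The strongest reply is that nothing stated is wrong. Under 1:1 randomization the unadjusted comparison is valid and unbiased, and its standard error already allows for chance imbalance. That stands: this is a point about efficiency.

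A second reply is that covariate lists and stratification factors belong in an analysis plan or full protocol not shown here. That holds for stratification, and its absence from the article is not a fault. It does not dispose of the analysis point, because the article names its tests and applies them to all endpoints. An adjusted primary analysis elsewhere would depart from that text.

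A third is that the gain is assumed. This also stands. The article gives no SD, between-centre variance or R². Without a scar score before surgery the usual strongest covariate is absent, and nothing shows that age, sex or BMI predict POSAS.

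A reader might go further and infer that the authors concede centre-to-centre variation, or that a centre term would remove the bias they mention. The text supports neither. The Discussion's remark concerns ligation and closure left to surgeons; it does not mention centres or the staff who administer the questionnaires. Closure is also chosen after allocation in an open-label trial and could differ between arms. A centre main effect would not correct that, and closure itself should not be entered as a baseline covariate.

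**Conclusion.** The point holds as an efficiency recommendation. The article fixes an unadjusted primary test in a multi-centre trial where a plausible driver of the outcome is left to the surgeon. A centre-adjusted model would use data already at hand.

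Before cost, the gain is about 2 to 9 points of power at two-sided 2.5% and about 2 to 6 at 5%, for R² between 5% and 20% and SD 5.0. With five added terms and no stratification, the net gain is about zero at R² of 5% and about 7 points (2.5%) or 5 points (5%) at 20%. If the terms explain almost nothing, about 2 points are lost. SD and R² are assumptions throughout.

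It would be too strong to say that the planned test is invalid, or that precision is demonstrably being wasted. That the plan is unadjusted is certain; how much adjustment would gain is not.

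**What to change.** Reword the Statistical analysis section so that the primary analysis is one prespecified linear model of 6-week POSAS on arm and centre, reporting the adjusted mean difference with its confidence interval. State before outcome data are examined how small centres are handled: pooled by a written rule, or centre as a random effect. Age, sex and BMI may be added as a short, fixed list. Given the break-even in step 3, the list should stay short. Exclude closure and ligation method, which are decided after allocation.

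Keep the present t or Mann-Whitney test as a sensitivity analysis, so that the provision for non-normal data is retained. If allocation was stratified by centre, say so and include centre for that reason.

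The change is to analysis wording only. It needs no further patients or data, and the named software can fit the model. The price is the small loss of precision shown above if centre and covariates turn out not to matter.

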**Methods and analysis::**

Patients diagnosed with appendicitis at the participating centers will be recruited and allocated into either a CLA or an SILA groups using a 1:1 randomization. Patients in the CLA group will receive a conventional 3-port laparoscopic appendectomy and patients in the SILA group will receive a laparoscopic appendectomy using a single-incision at the umbilicus. The primary trial endpoint is cosmetic satisfaction assessed using the Patients and Observer Scar Assessment Scale (POSAS) administered 6 weeks post-surgery. Secondary trial endpoints include cosmetic satisfaction assessed via the Body Image Questionnaire, pain levels assessed via the Visual Analog Scale and International Pain Outcomes questionnaire, and the presence of postoperative complications. The target sample size of this superiority trial is 120 patients, as this will provide 80% power at the 2.5% level of significance to detect a 3-point difference in POSAS.

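### The primary comparison is sized at a two-sided 2.5% level, but significance is declared at p < 0.05, so the stated 80% power and the decision rule do not match

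*Protocol article*

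**What the plan says.** Three places in the protocol article bear on the significance level of the primary comparison.

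- **Randomization and sample size calculation.** The target is 120 participants, allocated 1:1, and "this will provide 80% power at the 2.5% (two-sided) level of significance to detect a three-point difference in the POSAS score". The section adds that this number allows for 10% attrition.
- **Abstract, Methods and analysis.** The same claim appears without sidedness: "80% power at the 2.5% level of significance to detect a 3-point difference in POSAS". The trial is described there as a superiority trial.
- **Statistical analysis.** After covering the primary and secondary endpoints together, the section ends with one rule: "statistical significance will be declared for tests with p values < 0.05". It gives no separate threshold for the primary endpoint and does not say whether the p values are one- or two-sided.

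The Endpoints section names a single primary endpoint. The article describes no co-primary endpoint, alpha split, multiplicity adjustment or interim analysis.

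**The concern.** A power statement belongs to a particular test at a particular level. Here the level in the power statement is half the level in the decision rule, for the same comparison. The most familiar harmless explanation is that 2.5% one-sided is the same test as 5% two-sided. The sample size section closes that off as written, because it labels the 2.5% two-sided. So at least one statement needs to change: the label, the threshold, or the power figure.

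What is at stake is how a primary p value between 0.025 and 0.05 would be read. It meets the published decision rule but not the level at which the trial was designed. A reader could dispute a superiority claim resting on such a value by pointing to the protocol itself. The trial is also open-label, so the question should be settled while nobody has seen a between-group comparison.

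**Working it through.** **Inputs from the article.** Total 120, allocated 1:1; 10% attrition; difference of 3 points; power 80%; design alpha 2.5% two-sided; decision threshold 0.05; Student's t test if the data are normally distributed. Evaluable per arm: 120 × 0.9 / 2 = 54.

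**Input not given.** The article states no SD, so 120 cannot be reproduced forwards. The SDs below are back-calculated and are assumptions.

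**Critical values.** Two-sided 2.5%: z = 2.241. Two-sided 5%: z = 1.960. One-sided 2.5%: z = 1.960. For 80% power: z = 0.842. The last two critical values coincide; the first is a different test.

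**SD implied by 54 per arm.** For two means, SD = 3 × √(54/2) / (z_alpha + z_power), and 3 × √27 = 15.588.

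- Reading A, 2.5% two-sided as written: 15.588 / (2.241 + 0.842) = 5.06 (noncentral t: 5.00).
- Reading B, 2.5% per side, that is 5% two-sided: 15.588 / (1.960 + 0.842) = 5.56 (noncentral t: 5.51).

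In both cases 54 per arm is 108 evaluable, and 108 / 0.9 = 120. Both readings therefore lead to the stated target with similar SDs, so the target does not tell us which level was used.

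**Power when the level changes.** Once 80% is fixed at one level, the power at the other follows from the critical values. In the normal approximation it does not depend on the SD.

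- Sized at 2.5% two-sided, tested at 5% two-sided: Φ(3.083 − 1.960) = Φ(1.123) = 86.9% (noncentral t: 87.1%).
- Sized at 5% two-sided, tested at 2.5% two-sided: Φ(2.802 − 2.241) = Φ(0.560) = 71.2% (noncentral t: 71.0%).

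| Level used for sizing | Power if tested at two-sided 0.05 | Power if tested at two-sided 0.025 |
|---|---|---|
| 2.5% two-sided (A) | about 87% | 80% |
| 5% two-sided (B) | 80% | about 71% |

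**Sample size equivalents.** With n per arm = 2 × (z_alpha + z_power)² × (SD/3)²:

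- Under A (SD 5.06), 80% power at 0.05 needs 45 per arm, or 90 / 0.9 = 100 in total.
- Under B (SD 5.56), 80% power at 0.025 needs 66 per arm, or 132 / 0.9 = 146.7, rounded up to 147.

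**Size of the disputed band.** With no true difference, a two-sided p value falls between 0.025 and 0.05 with probability 0.05 − 0.025 = 2.5%. With a true 3-point difference, the probability is about 87.1 − 80 = 7% under A and 80 − 71.0 = 9% under B.

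**The case against.** The strongest reply is that the two statements have different jobs. The sample size section gives a design input; the Statistical analysis section gives the only decision rule in the article, and that rule is published in advance. Sizing at a stricter level than the one tested is odd and unexplained, but it is not impossible. This much stands: a p value of 0.03 would meet the only published decision rule, and it goes too far to say that the sample size section makes it a failure.

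It is also fair to say that the practical harm is limited. If p < 0.05 is applied as a two-sided rule, type I error is the conventional 5% and power is 80% or more on both readings. The abstract's 2.5% without sidedness is compatible with a simple mislabel. This stands too.

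A reader might infer more: that 120 is the wrong number, or that the trial is underpowered. The article does not support either. Without an SD the target can be neither confirmed nor refuted, and the 71% figure arises only if 0.025 is imposed on a trial that was really sized at 5% two-sided. Nor can the back-calculated SDs show which section is wrong, since they are derived from the very levels in dispute.

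The reply does not remove the inconsistency. Under A, 80% is not the power of the test that will be run. Under B, the stated two-sided level is wrong. A separate analysis plan could settle the threshold, but it would then have to depart from one of these published statements.

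**Conclusion.** The inconsistency is real and rests on the wording alone. Either the two-sided label in the sample size section is a slip for 2.5% per side, or the Statistical analysis section tests the primary endpoint at twice its design alpha (5% instead of 2.5%), with power of about 87% rather than 80%. The article does not say which.

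The power figures assume 54 evaluable per arm, a two-sample t test and two-sided p values. The fallback to a Mann-Whitney test was not modelled. The SDs of about 5.0 to 5.1 (A) and 5.5 to 5.6 (B) are assumptions from back-calculation.

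This should be corrected because it concerns the success criterion of the only primary endpoint. It does not invalidate the design: the sample size is not shown to be wrong, and under the published p < 0.05 rule the trial is not underpowered on either reading.

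**What to change.** Check which alpha and which sidedness were entered in the original calculation. Then make the abstract, the sample size section and the Statistical analysis section agree on one level for the primary endpoint, with sidedness stated. Do this before any comparative outcome data are examined; the trial is open-label, so unblinding is not a usable cut-off.

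- **If 2.5% two-sided was entered:** either state in the Statistical analysis section that the primary POSAS comparison is tested at two-sided 0.025, or keep two-sided 0.05 and restate the power as about 87%, with the abstract and sample size section amended to match.
- **If 2.5% per side was entered:** correct the abstract and the sample size section to 5% two-sided. The decision rule stays, with two-sided added.
- **If the calculation cannot be recovered:** choose one level in advance and disclose what follows. Two-sided 0.025 keeps the printed level, but has only about 71% power if the trial was really sized at 5% two-sided. Two-sided 0.05 has 80% or about 87% power, depending on how the trial was sized, and gives up the stricter printed level.

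The cost is a few words in up to three places and no additional patients. The one choice with a possible statistical price is the stricter threshold, for the reason just given.
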